## Abstract

**Background:**

Ocular massage has been reported to lower intraocular pressure (IOP) temporarily. This effect could be related to enhanced aqueous humor outflow; however, the mechanism is unclear.

**Objective:**

This study aims to examine the impact of digital and EyePeace ocular massage on IOP fluctuations and investigate whether the observed reduction in IOP is attributable to morphological changes in the Schlemm canal (SC).

**Methods:**

Participants were randomly assigned in a 1:1:1 ratio to 1 of 3 groups: digital ocular massage, EyePeace ocular massage, or no ocular massage. The primary outcome measure will be IOP. The secondary outcome measures will include anterior segment optical coherence tomography assessment of the SC and trabecular meshwork. In addition, adverse events in the quality of vision will be monitored and documented using a mobile app–based questionnaire. All assessments will be performed at baseline and 10 minutes after the assigned interventions.

**Results:**

Data collection was completed in the summer of 2025. The study results are expected to be published by the end of 2025.

**Conclusions:**

This study will investigate the impact of ocular massage on IOP and SC dimensions by using a randomized controlled design. As preliminary evidence suggests that ocular massage may transiently reduce IOP by enhancing aqueous humor outflow, this study will aim to clarify the underlying mechanism. By comparing digital ocular massage, EyePeace ocular massage, and no ocular massage, the study will assess changes in IOP and SC morphology. The findings are expected to provide insights into the role of mechanical manipulation in modulating aqueous humor outflow, potentially informing nonpharmacological strategies for possible glaucoma management.

**Trial Registration:**

Chinese Clinical Trial Registry ChiCTR2400093512; https://www.chictr.org.cn/showproj.html?proj=250459

**International Registered Report Identifier (IRRID):**

DERR1-10.2196/78864

## Introduction

### Background

Ocular massage has been recognized as a potential nonpharmacological technique to transiently reduce intraocular pressure (IOP) across various clinical scenarios. It has notably been used after glaucoma surgeries such as trabeculectomy to manage postoperative pressure fluctuations [1,2] presumably through the expansion of filtration blebs, enhancing aqueous humor drainage [3,4]. Moreover, ocular massage has shown efficacy in managing acute elevations of IOP after intravitreal injections and in acute angle-closure scenarios, demonstrating its versatility in ophthalmic practice [5,6].

In the setting of acute angle-closure attacks, patients can be instructed to perform ocular massage as an initial intervention to transiently lower IOP before definitive medical or surgical treatment can be administered [7,8]. Despite these promising clinical applications, previous studies have limitations that hinder drawing definitive conclusions about the underlying mechanisms and the sustained effectiveness of ocular massage [6,7]. Although the prior studies demonstrated temporary reductions in IOP after digital ocular massage, they were limited by the wide variability in the pressure applied by clinicians or patients and in the duration and frequency of massage because even small variations in finger placement or pressure can result in unpredictable IOP responses. These findings collectively highlight the potential clinical applications of ocular massage in various ophthalmic contexts [9]. EyePeace (Eye Comfort Ltd) is a commercially available device for eyelid massage designed to enhance meibum expression for dry eye disease related to meibomian gland dysfunction [10,11]. This flexible, handheld silicone device is used in conjunction with warm compress therapy and applies controlled vertical pressure to the closed eyelids [10,11]. EyePeace addresses the key limitations of manual digital ocular massage by offering a standardized, safe, and reproducible alternative. Unlike digital ocular massage, which is limited by inconsistent finger pressure, variable technique, and anatomical inaccuracy, EyePeace delivers calibrated and uniform mechanical force to the eyelids, ensuring consistent application across users and sessions. Its ergonomic design promotes proper positioning and motion, improving the reliability of therapeutic outcomes. By operating within safe pressure thresholds, EyePeace minimizes the risk of ocular complications such as hypotony, optic nerve stress, or retinal damage that may result from manual overcompression. In addition, its ease of use facilitates home-based therapy, enhancing patient adherence and long-term management. Originally developed for meibomian gland dysfunction, the device may also support aqueous humor outflow through gentle scleral compression, suggesting potential utility in select glaucoma settings. Overall, EyePeace offers a more controlled and patient-friendly approach that overcomes the variability and safety concerns associated with digital ocular massage.

IOP homeostasis is primarily dictated by the dynamic balance between aqueous humor production and outflow. The conventional drainage pathway involves the trabecular meshwork (TM), which directs aqueous humor into the Schlemm canal (SC) and then into aqueous and episcleral veins via collector channels [1,5]. A secondary, unconventional uveoscleral outflow pathway also contributes to aqueous humor clearance, albeit to a lesser extent [2,3,11-13]. Previous studies have provided insights into anatomical variations in aqueous humor drainage structures and their implications for IOP regulation [4,14]. Kagemann et al [15] reported that the cross-sectional area of the SC was significantly reduced in patients with glaucoma compared to healthy individuals, suggesting a structural contribution to elevated IOP [6,7,16,17]. Similarly, Chung et al [18] found that patients with newly diagnosed open-angle glaucoma who had larger baseline SC areas exhibited a more substantial IOP-lowering response to topical hypotensive agents, whereas TM width did not seem to influence the degree of pressure reduction. Advances in high-resolution imaging have now made it possible to visualize the corneoscleral region, including the SC and TM [19,20].

### Objectives

This study aims to evaluate changes in IOP after the use of the EyePeace ocular massager. We hypothesize that EyePeace will achieve a more consistent and pronounced IOP reduction compared to digital ocular massage. Furthermore, the observed IOP reduction may be correlated with morphological changes in underlying ocular structures.

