## Methods

### Study Design

This single-masked, randomized controlled trial will enroll 36 healthy Chinese participants (72 eyes) aged 18 years or older. They will be randomly assigned in a 1:1:1 ratio to the digital ocular massage group (24 eyes), EyePeace ocular massage group (24 eyes), or no ocular massage (24 eyes). The trial will be conducted at Tianjin Medical University Eye Hospital (TMUEH) in Tianjin, China, a nationally accredited clinical trial site. Healthy participants who voluntarily consent to undergo ocular massage will be invited to join this study to assess noninvasive clinical parameters. Patients and the public will not be involved in the design, implementation, reporting, or dissemination of this study. This study was registered on the Chinese Clinical Trial Registry (ChiCTR2400093512) on December 6, 2024.

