### Interventions

Eligible participants will be randomly assigned in a 1:1:1 ratio to (1) digital ocular massage (group A), (2) EyePeace ocular massage (group B), or (3) no ocular massage (group C). Group A and group B participants will receive ocular massage for 10 minutes [5,10,11]. Any participant experiencing an adverse event (AE) will be withdrawn from the trial, documented, provided appropriate treatment, and referred immediately to the principal investigator (PI). Clinical research staff will receive professional training covering participant enrollment, treatment procedures (including risks and benefits), and data collection processes. Participants will be sufficiently informed about the study and provided with compliance education to enhance participation and minimize noncompliance. Study staff will proactively contact participants in advance by telephone or SMS text message. EyePeace is a flexible, medical-grade silicone device designed to apply gentle, pulsatile vertical pressure to the closed eyelids. Although it does not contain a built-in pressure gauge, manufacturer specifications suggest that the applied force typically ranges from 0.2 to 0.5 N. To ensure consistency, all participants in the EyePeace ocular massage group received standardized instructions and a demonstration before use. In addition, a trained examiner supervised the massage procedure to ensure correct technique and duration. For the digital ocular massage group, clinical staff applied consistent fingertip pressure guided by prior training and feedback from pilot sessions, aiming to replicate the mechanical effect of the EyePeace ocular massage device. Although exact biomechanical equivalence between digital ocular massage and EyePeace ocular massage cannot be assured, the standardization procedures were designed to ensure comparability in massage duration, eyelid area coverage, and application frequency.

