### Sample Size

On the basis of the stated assumptions (a common SD of 1.9 and a maximum mean difference in IOP between groups of approximately 2 mmHg), a total of 36 participants (72 eyes [participants will contribute both eyes unless exclusion criteria apply]; 3 groups; 24 eyes per group) are required to achieve 90% power at α=.05 [1,5]. This corresponds to 3 groups of equal size in a randomized controlled trial. The calculations use a 1-way analysis of variance to test overall mean differences and consider a moderate to large effect size in IOP reduction. Allowing for a 10% dropout rate, the recruitment target is 40 participants (80 eyes). If further data refine the expected mean difference, the sample size will be adjusted accordingly (larger samples for smaller expected differences and vice versa).

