### Statistical Methods

Following the guidelines for statistical analysis plans in clinical trials [18,29], all statistical analyses will be conducted using SPSS software (version 25.0; IBM Corp). The significance level is set at 5% (2-tailed), with a 95% CI. The normality of data distribution will be assessed using the Shapiro-Wilk test. Data will be compared using 2-way repeated measures analysis of variance. If the hypothesis is unmet (*P*>.05), the Greenhouse-Geisser correction will be applied. Multiple comparisons will be made between groups at different time points using the Bonferroni-Holm correction. If the Shapiro-Wilk test indicates that the data are not normally distributed (*P*<.05), nonparametric tests will be used: paired comparisons will use the Wilcoxon signed-rank test, and between-group comparisons will use the Kruskal-Wallis H test. Statistical significance will be considered at *P*<.05 for 2-tailed tests unless otherwise specified. To ensure participant safety, the distribution of AEs will be described for both digital ocular massage and EyePeace ocular massage groups. The incidence rates of AEs were compared using the chi-square test or the Fisher exact test, as appropriate. An intention-to-treat analysis will be the primary analytic approach. All participants will be included in the analysis based on their original allocation, regardless of protocol adherence. For missing data, multiple imputation will be performed using the fully conditional specification method, assuming data are missing at random. A sensitivity analysis using a per-protocol approach will also be conducted to compare results. Given the short duration of this study, an interim analysis will not be performed.

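### The 90% power belongs to the overall three-group test and does not carry over to the stated EyePeace-versus-digital hypothesis; its consistency half has no planned comparison

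*Protocol article*

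**What the plan says.** The Objectives section of the protocol article states one directional hypothesis: "We hypothesize that EyePeace will achieve a more consistent and pronounced IOP reduction compared to digital ocular massage". It makes two claims about one pair of arms: a larger mean reduction, and a smaller spread.

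Sample Size rests on "a common SD of 1.9 and a maximum mean difference in IOP between groups of approximately 2 mmHg", and says that 36 participants (72 eyes, 24 per group) "are required to achieve 90% power at α=.05". It names the test: "The calculations use a 1-way analysis of variance to test overall mean differences". It gives neither an expected EyePeace-digital difference nor an inter-eye correlation, although participants contribute both eyes.

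Statistical Methods plans a two-way repeated measures analysis of variance, then between-group comparisons with Bonferroni-Holm correction, and Wilcoxon and Kruskal-Wallis tests if normality fails. Adverse-event rates are compared by chi-square or Fisher exact test.

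Interventions describes how the arms are delivered. In the digital arm, "clinical staff applied consistent fingertip pressure guided by prior training", with the aim of replicating the device's mechanical effect. EyePeace participants "received standardized instructions and a demonstration before use", and a trained examiner supervised the procedure. Results reports 50 participants recruited by July 15, 2025.

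**The concern.** The hypothesis and the sample size answer different questions. An overall F test asks whether any of the three means differ. A significant result can come entirely from massage versus no massage and need not bear on whether EyePeace beats digital massage. A reader who meets a single directional hypothesis and a single power figure will tend to join them. A non-significant EyePeace-digital result might then be read as evidence that the two are alike, when the trial had little chance of separating them.

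Consistency is a claim about variability. Every efficacy test listed compares location, so this half of the hypothesis cannot be answered by the analysis as described. The digital arm was also standardised towards the device, which narrows the difference in spread that the hypothesis concerns.

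**Working it through.** **Inputs from the article.** SD 1.9 mm Hg; largest difference 2 mm Hg; 24 eyes (12 participants) per group; two-sided 5%; Bonferroni-Holm for pairs; 50 recruited.

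**Assumptions, because the article is silent.** EyePeace-digital difference δ of 0.5 to 2.0 mm Hg; inter-eye correlation ρ of 0.5 to 0.9; 1.9 taken as the SD of the analysed IOP value for one eye.

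**1. Reproduce the stated size.** The noncentrality is λ = n Σ(μᵢ − μ̄)²/σ², referred to a noncentral F with 2 and 3(n − 1) degrees of freedom.
- Means 0/1/2: Σ = 2, so λ = 24 × 2/3.61 = 13.30. Power is 90.2%; 23 per group gives 88.8%. The stated 24 per group reproduces, with eyes treated as independent.
- Means 0/2/2 (EyePeace equals digital): Σ = 2.667, so λ = 24 × 2.667/3.61 = 17.73. Power is 96.6%.

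The second line shows that high overall power is compatible with no EyePeace-digital difference at all.

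**2. Power for the pair, unadjusted.** The mean of a participant's two eyes has SD s = 1.9 × √((1 + ρ)/2), which is 1.645 at ρ = 0.5 and 1.852 at ρ = 0.9. The noncentral t has noncentrality δ/(s√(2/12)) with 22 degrees of freedom. For δ = 1 this is 1/(1.645 × 0.408) = 1.49 at ρ = 0.5 and 1/(1.852 × 0.408) = 1.32 at ρ = 0.9.

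| δ (mm Hg) | 12 participants per arm, ρ 0.9 to 0.5 | 24 eyes per arm treated as independent |
|---|---|---|
| 0.5 | 10–11% | 14–15% |
| 1.0 | 24–30% | 43% |
| 1.5 | 48–57% | 76% |
| 2.0 | 72–81% | 95% |

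**3. Power for the pair under the planned Holm procedure.** Simulation with means 0/1/2 (no massage, digital, EyePeace), so δ = 1:
- 12 participants per arm, ρ 0.9 to 0.5: about 16–21%.
- 24 independent eyes per arm: about 34%.
- Under the same pattern, digital versus no massage is also a 1 mm Hg contrast and has the same power. EyePeace versus no massage (2 mm Hg) reaches about 54–66% with 12 participants per arm.

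**4. With the number recruited.** 50/3 = 16.7, so 16 or 17 per arm. Unadjusted power for 1 mm Hg is about 32–40% over the same range of ρ.

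**5. Spread.** For a two-sided F test of variances with 12 per arm and an SD ratio of 1.5, the upper critical value F(0.975; 11, 11) is 3.474. Power is P(F > 3.474/1.5²) = P(F > 1.544), about 24%.

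**The case against.** The strongest reply is that nothing in the article is false. Sample Size says openly that it tests overall differences, and the abstract's objective concerns the effect of both massages on IOP, which suits an overall test. The pair is analysed: with three groups, the Bonferroni-Holm comparisons necessarily include EyePeace versus digital. A fuller analysis plan may name key contrasts. The trial also recruited more than 36 participants.

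Much of this stands. A reader might infer that the mean contrast is not planned at all; Statistical Methods shows that it is. A reader might also take one low figure, such as the power at 1 mm Hg, as the trial's actual power for the hypothesis. The article does not support that, because it never states the middle mean. If EyePeace and digital were themselves the 2 mm Hg pair, power would be 95% with independent eyes, or 72–81% at participant level. That case requires digital massage to do no better than no massage, whereas the Introduction reports IOP reductions after digital massage.

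The delivery point also has limits. Training reduces finger-pressure variability but does not abolish it, and Interventions concedes that exact equivalence cannot be assured. That participants applied EyePeace themselves is an inference from the instructions and demonstration, not a statement.

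The mismatch between hypothesis and sizing remains, as does the absence of any described comparison of spread. Both arise from what the article itself states.

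**Conclusion.** The concern holds in a limited form. The 90% is correct for the overall test with eyes treated as independent and means equally spaced, but it says nothing about EyePeace versus digital. The mean contrast is planned but has no stated difference or power. The consistency claim has no matching analysis.

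The size is conditional. At participant level with 12 per arm and ρ of 0.5 to 0.9, no difference up to 2 mm Hg reaches 90% even without adjustment. At 1 mm Hg, power is 24–30% unadjusted and about 16–21% under Holm with means 0/1/2. The larger recruited number raises the unadjusted figure to about 32–40%, which is still low. These figures rest on the assumed δ and ρ and on SD 1.9 for a single eye.

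A reader might conclude that the size at least supports both massage-versus-control contrasts. It does not do so in general: under the equally spaced pattern that reproduces 24 per group, digital versus no massage is as weakly powered as EyePeace versus digital.

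**What to change.** 1. In Sample Size, state that 90% applies only to the overall test. Give participant-level power for EyePeace versus digital over a range of differences and inter-eye correlations, under the Holm procedure. Do not describe both massage-versus-control contrasts as supported by the stated size.
2. Report EyePeace versus digital as an estimated difference with a 95% CI, and state that a null result will not be read as equivalence.
3. Add a planned comparison of the spread of IOP change between the two massage arms: an SD ratio with CI, or a Brown-Forsythe test on participant-level change. Note its low power (about 24% for an SD ratio of 1.5 with 12 per arm). Otherwise, drop the consistency claim from the hypothesis.
4. Word the conclusion as a comparison of the massages as delivered: supervised EyePeace use versus digital massage by trained staff aiming to replicate the device.

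The cost is some rewording, one extra analysis and a less favourable stated power. Because data collection is reported as complete, the spread comparison should be fixed before unmasked results are seen, or labelled post hoc.

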## Methods

### Study Design

This single-masked, randomized controlled trial will enroll 36 healthy Chinese participants (72 eyes) aged 18 years or older. They will be randomly assigned in a 1:1:1 ratio to the digital ocular massage group (24 eyes), EyePeace ocular massage group (24 eyes), or no ocular massage (24 eyes). The trial will be conducted at Tianjin Medical University Eye Hospital (TMUEH) in Tianjin, China, a nationally accredited clinical trial site. Healthy participants who voluntarily consent to undergo ocular massage will be invited to join this study to assess noninvasive clinical parameters. Patients and the public will not be involved in the design, implementation, reporting, or dissemination of this study. This study was registered on the Chinese Clinical Trial Registry (ChiCTR2400093512) on December 6, 2024.

### Eligibility Criteria

The inclusion criteria were as follows: (1) age 18 years or older; (2) willingness to provide written informed consent, accept random allocation, and participate in ocular massage interventions, follow-ups, and assessments; and (3) IOP within the target range of 10 to 21 mm Hg. Patients were excluded based on the following criteria: (1) prior diagnosis of an eye disease, (2) history of ocular surgery, (3) current use of medications that might affect anterior segment ocular anatomy, (4) current contact lens wear, (5) history of ocular allergy, and (6) systemic disorders [21,22].

### Interventions

Eligible participants will be randomly assigned in a 1:1:1 ratio to (1) digital ocular massage (group A), (2) EyePeace ocular massage (group B), or (3) no ocular massage (group C). Group A and group B participants will receive ocular massage for 10 minutes [5,10,11]. Any participant experiencing an adverse event (AE) will be withdrawn from the trial, documented, provided appropriate treatment, and referred immediately to the principal investigator (PI). Clinical research staff will receive professional training covering participant enrollment, treatment procedures (including risks and benefits), and data collection processes. Participants will be sufficiently informed about the study and provided with compliance education to enhance participation and minimize noncompliance. Study staff will proactively contact participants in advance by telephone or SMS text message. EyePeace is a flexible, medical-grade silicone device designed to apply gentle, pulsatile vertical pressure to the closed eyelids. Although it does not contain a built-in pressure gauge, manufacturer specifications suggest that the applied force typically ranges from 0.2 to 0.5 N. To ensure consistency, all participants in the EyePeace ocular massage group received standardized instructions and a demonstration before use. In addition, a trained examiner supervised the massage procedure to ensure correct technique and duration. For the digital ocular massage group, clinical staff applied consistent fingertip pressure guided by prior training and feedback from pilot sessions, aiming to replicate the mechanical effect of the EyePeace ocular massage device. Although exact biomechanical equivalence between digital ocular massage and EyePeace ocular massage cannot be assured, the standardization procedures were designed to ensure comparability in massage duration, eyelid area coverage, and application frequency.

### Provisions for Posttrial Care

Participants who experience symptoms of conjunctivitis, keratitis, or other adverse reactions during the study or within 6 months after its completion will receive timely, targeted treatment. All such events will be documented in the AE record.

